*Phase 1 B: Health economic data sources and measurement*.** All consenting study participants will be asked asset ownership, house construction and demographic questions extracted from the most recent relevant national Demographic and Health Survey (DHS). Patient cost data will be captured before, during, and for 90 days after hospital admission using an amended version of the STOP-TB tool, a widely-used questionnaire for measuring TB patient costs
^
31
^. We will capture direct medical costs (
*e.g.*, drugs, diagnostics, consultation and inpatient fees), non-medical costs (
*e.g.*, food and transport), indirect costs (lost time for patients and guardians). Where a patient is readmitted to hospital, we will also capture these costs. Costs will be captured in local currency and presented in 2024 United States dollars.

Health system costs will be collected using top-down and bottom-up (micro) costing methods. We will develop and validate (with relevant hospital staff) a visual model of individual patient pathways through the study hospitals. This will be supplemented with data on waiting times, and time spent with various health workers from the sample of patients that are included in observations conducted as part of the situation analysis. Costs for each stage of the patient pathway (triage, admission, diagnostics, treatment, discharge, readmission
*etc*.) will be based on unit costs for tests, staff time, hospital bed days and other inputs, obtained from hospital data, tests and consumables suppliers, and Ministry of Health (MoH). Any other costs deemed relevant during the data collection stage will also be included. Top-down costing data on hospital overheads (utilities, building costs, maintenance,
*etc*.) will be obtained for each hospital.

HRQoL data will be collected using the EQ-5D-5L questionnaire in English, Chichewa (Malawi) and kiSwahili (Tanzania). The questionnaire will be administered, at admission, discharge, 30 and 90 days post admission in person or (day 30) by phone (as for patient costs).

**

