### Analysis

**
*Phase 1 A: Prospective longitudinal cohort study - quantitative statistical analysis*.** We will report the study in accordance with STROBE guidelines. A CONSORT diagram will summarise participant enrolment and follow-up. We will report descriptive statistics, including N (sample size of analysis population), n (sample size of analysis population without missing values). For continuous data we will report the mean and standard deviation for normally distributed data, or median and interquartile range for data that are not normally distributed. The proportion of observed levels will be reported for all binary and categorical measures alongside corresponding exact, binomial exact 95% confidence intervals (CIs) for proportions when appropriate. Results will be disaggregated by sex. Where appropriate, we will use multiple imputations using chained equations for missing data.

Will provide in-depth baseline epidemiologic and clinical management data across the different sites. Similarities and differences across sites will be recorded. Analysis will include evaluation of the association between clinical management and patient outcomes. Univariate and multivariate strength of association between variables and patient outcomes will be tested by logistic regression modelling.

Prevalences will be given as a proportion with 95% confidence intervals of the population estimate. Combinations of more than one will be assessed for their “joint prevalence” in order to understand multimorbidity disease clusters.

**
*Phase 1B: Health economic*.** Principle components analysis (PCA) will be used to construct wealth scores using individuals’ asset and other data, and wealth quintiles in the study population. Additionally, participants will be assigned to quintiles in reference to most recent DHS survey, allowing socioeconomic assessment of the study population relative to the national population.

Patient costs will be estimated for each individual patient including any costs incurred by their guardians in accompanying them to hospital or subsequent health care visits. Indirect costs (

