*e.g.*, lost time for paid or unpaid work, including housework) will be estimated based on the number of days of reported inability to work multiplied by the pre-disease wage given by patients during their baseline interview. The patient pathway model will be parameterised with unit costs and used to estimate individual patient and health system costs for a set of the most frequently observed multimorbidity combinations and patient types. Capital costs extending beyond one year will be annualised over their expected lifespan. Results will be presented as means and 95% confidence intervals. Deterministic and probabilistic sensitivity analyses will be conducted to test the robustness of the results. Multiple logistic regression will be used to compare patient costs by multimorbid condition(s) and wealth quintile to identify any significant differences. Additionally, we will examine the relationship between patient costs and age and sex. Change in HRQoL, expressed as QALYs, between admission, day 30 and day 90 interviews will be estimated using the area under the curve method. QALYs will be calculated according to the most relevant available tariff based on both geographical proximity and economic context. In our study we will use Uganda’s tariff for Tanzania, and Zimbabwe’s tariff for Malawi. Updated tariffs will be used if these become available before the analysis. The QALY calculations will also consider mortality during follow-up by attributing the lowest value from each value set (which corresponds to death), from the date of death until the end of the follow-up period. Missing patient cost or HRQoL data will be imputed using multiple chained imputations modelling with a predictive mean matching algorithm and relevant baseline variables.

Health economic analysis will be performed in Stata v15.4 and Excel.

**
*Phase 1 C: Situation analysis*.** Transcription and translation will be performed in line with local standard procedures. For accuracy, during the first 10 transcriptions a researcher will read the transcribed interviews and focus groups while listening to the audio recordings, and then check translations. Further checks will depend on the quality of these initial evaluations.

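### Indirect cost is meant to cover unpaid work and guardians' time, but its only valuation rule is the patient's own pre-disease wage

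*Protocol article*

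**What the plan says.** Three statements in the protocol article set the scope of indirect cost.

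- Data sources and measurement, Phase 1 B, lists "indirect costs (lost time for patients and guardians" among the patient costs to be captured, beside direct medical and non-medical costs.
- Analysis, Phase 1B, gives examples of what indirect costs include: "lost time for paid or unpaid work, including housework".
- The same section estimates each patient's costs "including any costs incurred by their guardians in accompanying them to hospital or subsequent health care visits".

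One statement sets the price. Indirect costs are "estimated based on the number of days of reported inability to work multiplied by the pre-disease wage given by patients during their baseline interview". The article states no guardian wage, replacement cost, minimum wage or other proxy for unpaid time.

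The resulting patient costs are to be compared by multimorbid condition and wealth quintile, and in addition "we will examine the relationship between patient costs and age and sex". Two general provisions follow: "Deterministic and probabilistic sensitivity analyses will be conducted to test the robustness of the results", and "Missing patient cost or HRQoL data will be imputed using multiple chained imputations modelling with a predictive mean matching algorithm and relevant baseline variables".

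**The concern.** The scope and the price do not fit together. Unpaid work carries no wage, so a rule that multiplies days by the patient's wage cannot value the housework that the same sentence includes. A guardian's lost day is not a day on which the patient was unable to work, and the guardian's time has no price of its own in the rule.

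Measuring economic costs is the primary health economic objective. A secondary objective breaks those costs down by multimorbidity and socio-economic factors. If the share of people without a wage differs between the groups compared, two groups that lose the same number of days will show different indirect costs because of earnings alone. Guardian time may not be small here: under Participants, Phase 1 C, the caregivers to be recruited are those who remain at the hospital throughout and look after the patient daily.

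**Working it through.** The plan gives no figure for indirect cost, so there is none to reproduce. The check has two parts: the rule applied literally, and an illustration of size under stated assumptions.

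**1. The rule applied literally**

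Indirect cost = days of inability to work × patient's wage.

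- Patient with a wage: the patient's own lost days are priced at that wage.
- Patient with no wage: days × 0 = 0, however many days are lost.
- Guardian days, reading A (only the patient's days enter): omitted.
- Guardian days, reading B (guardian days are added and multiplied by the patient's wage): priced at another person's wage.

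Under reading B the direction of error is not fixed. Take 10 guardian days, an earner's wage of 1 unit a day, and an unpaid day worth 0.5 (all assumed):

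- Waged patient, unwaged guardian: the rule gives 10 × 1 = 10, against 10 × 0.5 = 5, an overstatement.
- Unwaged patient, waged guardian: the rule gives 10 × 0 = 0, against 10 × 1 = 10, an understatement.

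**2. Size for patients' own time (assumed inputs)**

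Let s be the share of patients without a wage and w the value of an unpaid day relative to an earner's day. Days lost are taken as equal for earners and non-earners, and earners as having one common wage. The documents give neither s nor w.

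Understatement of mean patient indirect cost = s·w / [(1 − s) + s·w]

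| s | w | Calculation | Understatement |
|---|---|---|---|
| 0.3 | 0.5 | 0.15 / 0.85 | 18% |
| 0.3 | 1.0 | 0.30 / 1.00 | 30% |
| 0.6 | 0.5 | 0.30 / 0.70 | 43% |
| 0.6 | 1.0 | 0.60 / 1.00 | 60% |

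**3. Adding guardian time (a separate set of assumed inputs)**

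Assume 20 patient days and 10 guardian days, an earner's wage of 1, the same unwaged share u among patients and guardians, and unpaid time worth r of a wage.

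- Reading A: 20(1 − u)
- Reading B: 30(1 − u)
- Each person's own time valued: 30[(1 − u) + u·r]

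| u | r | A | B | Own time | A / own | B / own |
|---|---|---|---|---|---|---|
| 0.2 | 0.5 | 16 | 24 | 27 | 59% | 89% |
| 0.2 | 1.0 | 16 | 24 | 30 | 53% | 80% |
| 0.4 | 0.5 | 12 | 18 | 24 | 50% | 75% |
| 0.4 | 1.0 | 12 | 18 | 30 | 40% | 60% |
| 0.6 | 0.5 | 8 | 12 | 21 | 38% | 57% |
| 0.6 | 1.0 | 8 | 12 | 30 | 27% | 40% |

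The rule captures 27% to 59% of the cost under reading A and 40% to 89% under reading B. Reading B falls short in every row only because guardians are given the same wage mix as patients; part 1 shows that it can err the other way in individual pairs.

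**The case against.** The best defence is that the article is condensed. It nowhere says that non-earners are assigned a wage of zero, and since it expressly includes housework, some wage equivalent may be intended. Costs are collected with an amended version of an existing questionnaire, which may record guardian income or a proxy wage. A patient who gives no wage might be treated as missing and imputed, and sensitivity analyses are already promised.

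Part of this stands. The questionnaire may hold usable data, and the intention may be sound. It does not settle the point, for three reasons.

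- The questionnaire governs what is captured; the article itself fixes the formula, and that formula names only the patient's wage.
- A true wage of zero is an observed value, so imputation of missing data does not reach it. The article does not say that having no wage is coded as missing.
- The sensitivity analyses name no alternative valuation, and scaling a zero wage up or down leaves it at zero.

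A reader might go further and infer that the rule makes women, older people and the poorest look nearly cost-free, so that the planned comparisons measure wages and not illness. The documents do not support that. They give no wage data by sex, age or wealth. Direct medical and non-medical costs are untouched by the rule. Nothing shows that indirect cost dominates the total, or that wage status differs by multimorbidity. Nor do they support a claim that guardian time is always undervalued.

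**Conclusion.** The point holds as a mismatch between a stated scope and a stated rule, and should be corrected before analysis. Followed literally, the rule gives an unwaged patient's lost days no value and gives guardian days no price of their own. It affects the indirect component of patient cost, and comparisons by wealth quintile, age and sex to the extent that wage status differs across those groups, which is an assumption.

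The size cannot be derived from the documents. The 18% to 60% range rests entirely on the assumed shares and relative values, concerns mean patient indirect cost and not total patient cost, and leaves guardians out. For guardian time, neither size nor direction is determined.

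**What to change.** In Analysis, Phase 1B:

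- Keep the reported pre-disease wage for patients who earn.
- Value non-earners' lost days at a stated proxy wage for each country. Use the same proxy for guardian days where no guardian wage was collected.
- Within the sensitivity analyses already planned, vary the proxy, for example 0%, 50% and 100% of the chosen value. For unwaged patients, 0% reproduces the present rule.
- Report indirect cost separately from direct cost, and by earner status where the data allow.

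The cost is one external wage figure per country, some extra runs, and one added valuation assumption that the sensitivity analysis makes visible. Study status says that the analysis has not been performed and the code is still being developed, so the change is timely. It also says that the study is already in follow-up: a split of lost days into paid and unpaid may not be recoverable if the interviews did not record it, so the fix should not depend on one.

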### Objectives

The primary objectives of this mixed methods (clinical, health economics and qualitative) study are:

*Clinical:* Determine the prevalence of multimorbid disease in adults admitted to hospital with acute medical conditions in Malawi and Tanzania.

*Health Economic:* Measure economic costs incurred and changes in health-related quality of life between admission and 90 days post admission.

*Situation analysis:* Describe current care for multimorbidity, enabling and hindering factors to the delivery of patient centred care.

We aim to use the findings to inform the development and design of a randomised controlled trial.

The secondary objectives are:

*Clinical:*

1.Measure prevalence of important pre-selected individual conditions, including chronic non-communicable (hypertension, diabetes mellitus and chronic kidney disease) and communicable (HIV infection) conditions.2.Measure hospital readmission rate 30 and 90 days after admission.3.Measure survival 30 and 90 days after admission.4.Measure a composite of readmission free survival 30 and 90 days after admission.5.Measure markers of disease control 90 days after admission.6.Measure the rate of end-organ damage (such as cerebrovascular accident and myocardial infarction).

*Health Economic:*

1.Disaggregate economic costs from patient and health system perspectives and sub-analyse according to the presence of multimorbidity and other socio-economic factors.2.Model how patients with different multimorbidity incur costs as they pass through the health system.3.Analyse changes in Health-related Quality of Life according to presence of different diseases.4.Estimate the potential cost-effectiveness of a selected intervention to improve diagnosis and treatment for people with multimorbidity.

*Situation Analysis:*

1.Describe healthcare pathways for adults during and after acute medical admission using structured observational data during patient admission.2.Qualitatively describe (i) patients’ level of health literacy related to their own conditions and (ii) healthcare engagement for patients with multimorbidity using key-informant interviews.

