### Sample size

**
*Phase 1 A: Prospective longitudinal cohort study*.** The primary outcome will be disease prevalence. At 5% prevalence, a precision of 1.5% and power of 90% at α=0.05 is expected (precision will reduce as actual estimate rises towards 50%). We will use 5% prevalence as the lower boundary for inclusion of the disease during intervention development. We expect that HIV, hypertension and diabetes will meet this threshold. The cohort will allow us confidence to decide on the inclusion of chronic kidney disease. Prevalence will be assessed in both countries at the district and central hospital level to determine if findings are shared across settings. Given these assumptions, sample size is 1544 patients, with a target of 1600 to account for drop out. We will recruit these patients across the four hospitals (with numbers varying between sites due to different patient loads).

**
*Phase 1 B: Health economic evaluation*.** A randomised sub-sample of one third of the cohort study participants will be selected for participation in patient costing and HRQoL analysis (approximately 133 participants per hospital).

**
*Phase 1 C: Situation analysis*.** Sampling strategies for patients and caregivers is designed to include those individuals representing: those admitted for the first time and those who are returnees; those on HDU, ICU and ordinary wards; different age categories; male and female. We will ensure inclusion of patients with multiple known pathologies representing “multimorbidity” according to the final definition. Sample sizes for interviews are preliminary; they will continue until a point of saturation is reached.
Table 2 shows estimates of the number of patient and carer interviews required. For healthcare workers, we will include different cadres working in different departments.

**Table 2. T2:** Number of in-depth interviews, focus group discussions and structured discussions.

PER HOSPITAL SITE	In-depth interviews	Focussed group discussions	Structured discussions
Patients with multimorbidity *	10	24	10
Caregivers to patients with multimorbidity *	10	24	10
Doctors	2	-	4
Nurses	4	-	8
Ward attendants	2	-	6
Reception / frontline administration staff	2	-	2
Total	30	48	40

* Patients and caregivers will not be the same group during IDIs and FGDs. IDI, In depth interviews; FGD, focus group discussion.

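### Logistic regression is named for comparing patient costs, but cost is a dollar amount and no binary cost outcome is defined, so the model does not estimate the cost difference sought

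*Protocol article*

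**What the plan says.** The health economic paragraphs of the Analysis section give one regression method for patient costs: "Multiple logistic regression will be used to compare patient costs by multimorbid condition(s) and wealth quintile to identify any significant differences".

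The rest of the article treats the same outcome as continuous money:

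- Unit (Data sources and measurement): "Costs will be captured in local currency and presented in 2024 United States dollars".
- Level (Analysis): "Patient costs will be estimated for each individual patient including any costs incurred by their guardians". The indirect part is days unable to work multiplied by a wage.
- Summary (Analysis): "Results will be presented as means and 95% confidence intervals".
- Missing data (Analysis): "Missing patient cost or HRQoL data will be imputed using multiple chained imputations modelling with a predictive mean matching algorithm and relevant baseline variables". Predictive mean matching draws observed numeric values.

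The objective served is the first secondary health economic one: "Disaggregate economic costs from patient and health system perspectives and sub-analyse according to the presence of multimorbidity and other socio-economic factors". The data come from a third of the cohort (Sample size): "A randomised sub-sample of one third of the cohort study participants will be selected for participation in patient costing and HRQoL analysis", stated as "approximately 133 participants per hospital".

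**The concern.** Logistic regression models the probability of a binary event. The article defines no such event for cost: no threshold, median split or catastrophic-cost definition. The analyst must therefore either turn cost into a yes/no variable at a level that the article does not fix, or depart from the stated method.

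If cost is cut, the result answers a different question: whether patients with a given condition or wealth level are more often above the cut, not how much more they spend. A few very expensive admissions could move mean cost a good deal and leave the odds ratio almost unchanged. The odds ratio also could not be set beside the reported means. With no cut-point fixed, the level could be chosen after the costs have been seen.

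**Working it through.** **1. The plan's own figure.** Target cohort 1600, one third, four hospitals: 1600 / 3 = 533 in total, and 533.3 / 4 = 133.3 per hospital. This reproduces the stated 133. No effect size or power is stated for the cost comparison.

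**2. What the stated model estimates.** For patient cost Y, group x and cut c, logistic regression gives the log odds ratio for Y > c. The objective and the reporting rule concern E(Y). The two differ, and the link between them depends on c and on the spread of costs.

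To show by how much, assume lognormal costs (the article gives no distribution) with equal log-scale SD in both groups and a true mean ratio of 1.30, so ln 1.30 = 0.262. Place the cut at a quantile of the reference group, with standard normal value z. The share above the cut in the other group is 1 − Φ(z − 0.262/SD).

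| Cut in reference group | Log-SD | Share above, reference | Share above, other group | Odds ratio |
|---|---|---|---|---|
| Median (z = 0) | 1.0 | 0.500 | 0.603 | 1.52 |
| Median | 1.5 | 0.500 | 0.569 | 1.32 |
| 80th percentile (z = 0.842) | 1.0 | 0.200 | 0.281 | 1.56 |
| 80th percentile | 1.5 | 0.200 | 0.252 | 1.35 |

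The same ratio of mean costs gives odds ratios from 1.32 to 1.56. A reader cannot recover the mean ratio, or a dollar difference, from the odds ratio alone.

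**3. Is power a second ground?** Simulated power, N = 533, two-sided 5%, lognormal costs. The multimorbid share, log-SD and ratio are assumptions. The 20% rows are unadjusted; the 30% rows adjust for wealth quintile. A dash means that no figure is given here.

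| Multimorbid share | Log-SD | Mean ratio | Regression on log cost | Median-cut logistic | Gamma log-link GLM, robust SE | Raw-cost linear, robust SE |
|---|---|---|---|---|---|---|
| 20% | 1.0 | 1.30 | 70% | 51% | 50% | 42% |
| 20% | 1.5 | 1.50 | – | 51% | 35% | – |
| 30% | 1.0 | 1.30 | 80% | 60% | 64% | – |
| 30% | 1.5 | 1.49 | 80% | 59% | 52% | – |

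Repeat runs of the 20% rows moved these figures by about 2 to 3 points. Against log-cost regression, cutting at the median loses about 20 points. The large-sample efficiency is φ(0)² / (0.5 × 0.5) = 0.64, so 533 patients carry the information of about 339. But log-cost regression tests on the log scale and targets geometric means unless retransformed. Against models that estimate mean cost directly, the median-cut logistic model has similar or higher power in three of the four rows and is 4 points behind in the other. With sandwich standard errors, the gamma model's type I error at a nominal 5% was about 6% to 7% at log-SD 1 and 8% to 9% at log-SD 1.5.

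**The case against.** **The sentence may be a slip, or an abbreviation.** The word linear may have been intended, or a binary cost outcome may be defined in a fuller protocol or analysis plan; an article can leave a cut-point to those. This is fair as an explanation, but it does not clear the text. The article does not leave the model open: it names one that does not fit the outcome as it describes it. On either reading the sentence needs correcting.

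**Mean costs will be reported anyway.** This stands in part. Means with 95% confidence intervals are planned, and the pathway model is to estimate costs for frequent multimorbidity combinations. The primary health economic objective of measuring costs does not rest on this regression. What is affected is the regression comparison by condition and wealth quintile, under a secondary objective.

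**A reader might infer that the main harm is lost power.** The calculations do not support that in general. The gain appears against log-cost regression on data generated as lognormal, which is that model's best case. It does not carry over to mean-cost models. The article also never says that costs are skewed; that is a reasonable assumption, but the mismatch does not depend on it.

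**A reader might also infer that odds ratios would break the pathway or cost-effectiveness model.** The article does not support this. The pathway model is parameterised with unit costs from hospitals, suppliers and the Ministry of Health, and the regression is nowhere named as an input.

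**Conclusion.** The point holds on the estimand. The article names a model for a binary outcome, defines cost as a continuous dollar amount, and gives no binary version. As written, the analysis does not estimate the difference or ratio in mean cost by condition and wealth quintile, and it leaves a cut-point open.

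This conclusion needs no distributional assumption. Its illustrated size (odds ratios of 1.32 to 1.56 for one mean ratio of 1.30) assumes lognormal costs with log-SD 1 to 1.5 and a cut at the reference median or 80th percentile. No general claim about power follows.

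This should be fixed, but it is not critical: it touches a secondary health economic analysis, and neither the prevalence outcome nor the planned cost summaries depend on it.

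**What to change.** Replace the sentence with a regression for continuous patient cost. Two suitable choices are linear regression with bootstrap confidence intervals, or a log-link generalised linear model with the family checked against the data and bootstrap intervals. Bootstrap intervals are suggested because sandwich standard errors gave inflated type I error under heavy skew. Report adjusted mean differences in US dollars, or ratios of means, by multimorbid condition(s) and wealth quintile. The planned look at age and sex can use the same model.

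If a binary cost outcome is wanted as well, define and justify its threshold before analysis and use logistic regression for that outcome only.

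The cost is a change of wording and code. The Study status section says that code is still being developed and no analysis has been done, so nothing has to be repeated and no new data are needed.

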**Primary objectives:**

Clinical: Determine prevalence of multimorbid disease among adult medical admissions and measure patient outcomes. Health Economic: Measure economic costs incurred and changes in health-related quality of life (HRQoL) at 90 days post-admission. Situation analysis: Qualitatively describe pathways of patients with multimorbidity through the health system.

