**Methods:**

This is a prospective longitudinal cohort study of adult (≥18 years) acute medical hospital admissions with nested health economic and situation analysis in four hospitals: 1) Queen Elizabeth Central Hospital, Blantyre, Malawi; 2) Chiradzulu District Hospital, Malawi; 3) Hai District Hospital, Boma Ng’ombe, Tanzania; 4) Muhimbili National Hospital, Dar-es-Salaam, Tanzania. Follow-up duration will be 90 days from hospital admission. We will use consecutive recruitment within 24 hours of emergency presentation and stratified recruitment across four sites. We will use point-of-care tests to refine estimates of disease pathology. We will conduct qualitative interviews with patients, caregivers, healthcare providers and policymakers; focus group discussions with patients and caregivers, and observations of hospital care pathways.

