### Variables

**
*Phase 1 A: Prospective longitudinal cohort study*.** The main outcome is to define the characteristics of multimorbidity. We will employ enhanced point of care test (POC) diagnostics for patients admitted to the study to determine the prevalence of multimorbid diseases of interest (specifically HIV, hypertension, diabetes and chronic kidney disease). All POCs used in the study are CE marked and commercially available. We will make the results of these tests available to treating healthcare providers using a standardised proforma. No treatment recommendation will be provided with this information and clinicians will be able to interpret and use this information independently. Structured data extraction of clinical information (including potential predictors of patient outcomes) will be performed at intervals (described in
Table 1 from patient records.

**
*Phase 1 B: Health economic evaluation*.** To explore the impact of socioeconomic status (SES) on patient costs, clinical outcomes and health-related quality of life (HRQoL) we will calculate wealth scores and use these to assign all clinical cohort study participants to SES quintiles. For participants randomised to the health economic study, we will collect data on patient costs at admission (in person), discharge (in person), 30 and 90 days post discharge (in person or by telephone). Health system costs for patients in the cohort study will be modelled using top down and bottom up costing methods. HRQoL will be estimated in quality adjusted life years (QALYs).

**
*Phase 1 C: Situation analysis*
** In depth interviews (IDI) and focus group discussions (FGD) with patients recruited to the cohort study, and their care givers will be conducted to understand their experiences, preferences, and priorities, including level of health literacy and engagement with healthcare providers for long term management of chronic conditions. Exploration of detailed experiences from patients and carers will provide specific concrete examples of their expectations, and any concerns they have, as well as their priorities and perceptions of how the hospital currently manages acute medical patients with multimorbidity, problems and how best to address them.

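### The plan labels area-under-the-curve QALYs as change in quality of life; read literally, this measures QALYs accrued over 90 days, not the admission-to-day-90 change in the objectives

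*Protocol article*

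**What the plan says.** The Objectives section gives the primary health economic objective as "Measure economic costs incurred and changes in health-related quality of life between admission and 90 days post admission". The abstract states the same aim. Secondary health economic objective 3 is "Analyse changes in Health-related Quality of Life according to presence of different diseases".

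The Variables section (Phase 1 B) puts HRQoL on the QALY scale and names no other. The Analysis section (Phase 1B) then gives the estimator: "Change in HRQoL, expressed as QALYs, between admission, day 30 and day 90 interviews will be estimated using the area under the curve method". It adds a rule for deaths: "The QALY calculations will also consider mortality during follow-up by attributing the lowest value from each value set", applied from the date of death to the end of follow-up.

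The article does not mention a difference in utility between visits, a subtraction of admission utility, or a model that adjusts for it.

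**The concern.** A change from admission to day 90 compares two states of the same patient. An area under the utility curve adds up the level of utility over the period. The plan attaches the name of the first to the calculation of the second.

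The difference matters in this cohort because patients are recruited within 24 hours of emergency presentation. The admission value is therefore taken during acute illness and may well differ between disease groups. In a change score, a low admission value increases the apparent recovery. In an area under the curve, it lowers the total.

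Under a literal reading, a disease group could appear to have less change only because its members were sicker on arrival. Groups with different recovery could also appear alike. The result at stake is the one reported for a primary objective and for its breakdown by disease.

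**Working it through.** The plan states no effect size, standard deviation or power for this objective, so there is no figure to reproduce. The check takes the visit times from the Analysis section (admission, day 30, day 90) and the 90-day follow-up from the abstract. The article gives no utilities, so those below are assumptions for illustration.

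**Formula.** Let u0, u30 and u90 be utility at admission, day 30 and day 90. The trapezoidal area, in years, is

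QALY = [30 × (u0 + u30)/2 + 60 × (u30 + u90)/2] / 365 = (15·u0 + 45·u30 + 30·u90) / 365.

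As shares of the 90 days, the weights are 15/90 = 1/6, 45/90 = 1/2 and 30/90 = 1/3. All are positive. The change to day 90 is u90 − u0, in which admission utility has a negative sign and day 30 does not appear. The largest possible total, at utility 1 throughout, is 90/365 = 0.2466 QALY.

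**Same QALYs, different change.**
- Patient A, 0.2 / 0.6 / 0.8: (3 + 27 + 24)/365 = 54/365 = 0.1479 QALY; change = 0.8 − 0.2 = +0.6.
- Patient B, 0.6 throughout: 0.6 × 90/365 = 54/365 = 0.1479 QALY; change = 0.

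**Same change, different QALYs.**
- Stable at 0.4: 36/365 = 0.0986 QALY; change = 0.
- Stable at 0.9: 81/365 = 0.2219 QALY; change = 0.

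**If admission utility is subtracted.** The QALY gain is then QALY − u0 × 90/365.
- Patient A: 0.1479 − 0.2 × 90/365 = 0.1479 − 0.0493 = +0.0986.
- Patient B and both stable patients: 0.

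This version separates A from B and gives the stable patients the same value. It is a time-averaged gain and need not agree with the day-90 difference. For 0.60 / 0.333 / 1.00 the area is (9 + 15 + 30)/365 = 0.1479 and the subtraction is 0.60 × 90/365 = 0.1479. The gain is therefore 0, although utility at day 90 is 0.40 above admission.

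**The case against.** The strongest reply is that the sentence can be read as a QALY gain over admission, that is, the area minus u0 × 90/365. On that reading the example of A and B no longer shows a fault, as the working confirms. The objective also does not say whether change means an endpoint difference or a time-averaged one. This stands to the extent that the authors may intend it. The article does not state it, however, and an analyst who follows the text as printed would report accrued QALYs under the name of change.

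A second reply is that a condensed article leaves baseline adjustment, covariates and group models to an analysis plan. That is right for those details, and their absence is not the point here. The point is that the article names an estimator for a stated objective, and the two do not match as written.

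Three stronger readings are tempting, and the documents do not support them.
- A reader might infer that the area under the curve cannot in general tell recovery from no change. Equal totals need different admission levels or a dip at day 30. With the same admission value and steady improvement, the area exceeds that of a stable patient.
- A reader might infer that the cost-effectiveness modelling is compromised. Accrued QALYs are a suitable input there, and the threshold for including a disease in the intervention is prevalence of at least 5%, not change in HRQoL.
- A reader might infer that comparisons between disease groups are certain to be confounded by severity on arrival. The article specifies no between-group HRQoL model, so this is a risk under an unadjusted comparison and not a demonstrated error.

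A simple difference in utility also has a weakness. The plan's QALY calculation takes deaths into account, whereas a difference has no value for a patient who dies before the visit unless one is assigned.

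**Conclusion.** The point holds as a mismatch between objective and stated estimator. Read literally, the Analysis section answers the primary HRQoL objective and secondary objective 3 with QALYs accrued over 90 days, which is a level and not a change.

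The size can only be illustrated. Equal totals of 0.148 QALY can go with changes of +0.6 and 0, and equal changes of 0 can go with 0.099 and 0.222 QALY. These figures rest on assumed utilities and on trapezoidal interpolation between the three visits. Nothing in the article shows how often such patterns will occur, so it is not established that the study's conclusions would be wrong. If a baseline-subtracted gain is intended, what remains is that the formula must be stated and the result described as a time-averaged gain.

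**What to change.** - For the change objectives, report EQ-5D utility at each visit, with the day-30 and day-90 values minus admission, overall and by disease group.
- State how deaths before each visit are valued. One option is to carry the plan's own death value into the difference and show a survivors-only result alongside.
- Rename the area-under-the-curve result QALYs accrued over 90 days, and keep it for the cost-effectiveness modelling. If a QALY gain is intended, define it as the area minus admission utility × 90/365.
- Present a model of follow-up utility adjusted for admission utility as a supporting analysis only. The disease groups are not randomised, and disease may itself affect the admission value, so this adjustment is open to debate as the main comparison.
- Note in the report that the overall rise includes recovery from the acute illness.

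The cost is some extra analysis and one explicit assumption about the value at death. EQ-5D-5L is already scheduled at admission, day 30 and day 90. The Study status section says that analysis has not yet been performed, so the change can still be made without new data collection.
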